The response of the different components of stress-response systems can be measured using various biomarkers, such as cortisol and α-amylase [15]. Cortisol is a marker of the HPA axis [6,16]. Cortisol and α-amylase levels show an opposite rhythm throughout the day. Cortisol decreases during the day and increases at night; for α-amylase, vice versa [17]. Cortisol shows a peak approximately half an hour after awakening, whereas α-amylase typically declines at that time [17]. Cortisol concentrations then decrease throughout the day, whereas α-amylase increases and shows a peak late in the afternoon or in the evening [18]. Cortisol levels may fluctuate due to pulsatile secretion, the diurnal rhythm, and acute stress [19].

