## 2. Materials and Methods

### 2.1. Design

This study is a part of the large, multinational cluster-randomized controlled trial Music Interventions for Dementia and Depression in ELderly care (MIDDEL) (ClinicalTrials.gov registration NCT03496675) [1]. In the present exploratory substudy, participants from all four arms (GMT, RCS, GMT plus RCS, or control group) of the original trial from Norway, Germany, and the Netherlands were included (Figure 1). For the part of the substudy addressing immediate effects using saliva samples, only three arms (GMT, RCS, control group) were included. This limits participant burden and prevents uncertainty about which music intervention may have caused a certain effect in the combination group receiving both GMT and RCS. The primary outcome of the main trial was depressive symptoms at 6 months, measured with the MADRS [2]. For additional information about the main trial, study design, and procedures, see Gold et al., 2019 [1].

Chronic stress can be assessed objectively from cortisol in hair samples, as hair cortisol (HC) provides insight into cortisol levels over a longer period of time [4,25]. Sampling HC is an objective, easy, non-invasive, and affordable way of assessing chronic stress in people with dementia [19,24,25]. HC represents the longer-term retrospective activity of the HPA axis, which, in turn, is associated with chronic stress [31].

Measuring cortisol and α-amylase in the saliva is a non-invasive, easy, and reliable way to assess stress on health outcomes [3,4,5]. Assessment of stress in SC concerns real-time data, and especially in times of stress, there are significant correlations between cortisol concentrations in saliva and blood [4]. The digestive enzyme α-amylase can be measured from the same saliva sample to assess stress [5]. To date, SAA has only been assessed in a few clinical samples [5]. Hence, by examining both biomarkers—which can conveniently be analyzed with the same sample—a more complete picture of immediate physiological stress can be obtained [32].

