#### 2.6.3. Secondary Study Parameters: Salivary Cortisol and Alpha-Amylase

SC can provide more insight into how well the endocrine stress system responds to an immediate intervention because HC does not provide insight into how well the HPA axis functions. As residents with depressive symptoms were expected to have steeper cortisol slopes, we hypothesized that participants have a higher SC before the start of the music session, and participating in the music intervention attenuates the SC. Samples were collected on days a music or book reading session took place, between 12.00 and 17.00 h, preferably at 15.00 h, to minimize any confounding effects of the diurnal hormonal rhythm. In order to assess the immediate effects of music interventions on stress, saliva samples were collected to assess SC and SAA levels just before, 15 min after, and 60 min after the music/book reading session. Multiple measurements of SC and SAA per resident were required because of variations in levels over time within residents [15]. The assessment took place at T1 (within 1 month after the music interventions started or within 1 month after completion of the baseline assessment in the control group), T3 (3 months), and T6 (6 months). The days were selected according to logistic convenience (the first session that took around 15.00 h around T1, T3, and T6 were selected).

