### 2.9. Sample Size and Power

Through convenience sampling, a subsample of residents from three countries (the Netherlands, Germany, and Norway) from the MIDDEL trial was asked to participate in this substudy. The aim was to include 50 care home residents in every group (GMT, RCS, GMT plus RCS, control group at baseline). The Netherlands and Germany aimed to include 8 CHUs/80 participants each, and Norway aimed to include 4 CHUs/40 residents. Attrition of residents was expected to occur due to mortality, moving to another care home, or refraining from participation in the substudy. The mean length of stay in a care home in the Netherlands is 8 to 12 months. A mortality rate of 20% within the intervention period of 6 months (primary outcome at 6 months) was taken into account with respect to the sample size. Mortality is lower in care home residents with mild to moderately severe dementia (compared to severe and very severe). The power for this exploratory substudy with this given sample size was difficult to determine because there are no previous studies or agreed minimal clinically important difference for this combination of intervention, population, and outcome. As in the MIDDEL protocol [1], the main effects in this substudy were tested as GMT versus no GMT and RCS versus no RCS so that all participants with available data could be used in each test. Thus, after a dropout of 20% until the primary endpoint of 6 months, as assumed in the MIDDEL protocol, we expected to have 160 participants in total. Compared to the MADRS, we expected the cluster effect in these biological indicators to be smaller, with an ICC ≤ 0.01. The average cluster size after 20% dropout will be eight. Because there are two main comparisons, tests were Bonferroni-corrected from 5% to 2.5%, two-sided. We used R to determine the effect size for which 80% power is reached with a two-sample *t*-test with 160 participants in total, adjusted for clustering, with a two-sided 2.5% significance level, and found that the effect size that can be reliably determined with this substudy is d = 0.51, i.e., a medium effect size [51]. This seems reasonable compared to previous studies of music therapy [14,52]. The actual power may be higher in a longitudinal model if time points are correlated.

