#### 2.10.2. Secondary Study Parameters

In the final model in which MADRS scores at the endpoints (3 and 6 months) are predicted by the therapy group (Gold et al., 2019), baseline stress was added to examine whether chronic stress (HC concentrations; perceived stress) predicts the treatment effect. Secondary study parameters were added to the final model. A description of the effect of amylase response (expected to change at 15 min), cortisol response (expected to change at 60 min), and experienced stress (assessed with the VAS) were provided. Correlation of stress biomarker response (SC and SAA levels at T3 and T6, pre-post treatment) and change in MADRS score (T3–T0 and T6–T0) were examined. The design was able to account for between-group variation (including differential responses in three groups) and within-group variation (changes in participants between 3 months, 6 months, and baseline).

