### 2.11. Statistical Analyses

Data were analyzed using SPSS Statistics version 26. Immediate and chronic stress were assessed with psychological subjective indicators of stress and physiological markers of stress. Descriptive statistics (mean, standard deviation, range) were calculated for demographics, the PSS, and VAS scores for all time points. Power calculations were computed. In addition, we reported effect size estimates. The distribution was assessed, and if needed, data were log-transformed to be normally distributed accordingly, especially since cortisol and SAA data may have a positively skewed distribution.

The effect of repeated music interventions on chronic stress was measured with the biomarker HC. HC concentrations were reported in pg/mg. Concentrations of HC at baseline were assessed as a predictor of treatment response. In order to assess the association between the HC concentration and perceived stress (PSS-10), correlations were computed. Changes in HC concentrations over time and perceived stress (PSS-10) were assessed. The levels of stress after 3 and 6 months were modeled to account for differences in therapy: RCS compared to control (usual care or book reading), GMT to control, GMT + RCS, and baseline differences in stress (T0). In the final model, in which MADRS scores at the endpoints (3 and 6 months) were predicted by the therapy group, baseline stress was added to observe whether there was a change in treatment effect. The analyses included a correlation between stress reduction (at T3, pre-post treatment) and change in MADRS score (T6–T3–T0).

SC and SAA were concomitantly measured and were used as outcome measures to assess whether changes in activity in the HPA axis and the ANS axis occurred pre- and post-intervention. Pre- and post-sampling weight of saliva samples were measured. Levels of SC were reported in nmol/L and levels of SAA in U/mL. Adherence to instructions prior to the collection of the saliva sample was assessed. A description of the effect of SAA response (expected to change at 15 min) and SC response (expected to change at 60 min) was provided. The design is able to account for between-group variation (including differential responses in four groups) and within-group variation (changes in participants between 3months, 6 months, and baseline). Exploratory subgroup analyses and moderator analyses were performed.

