## Figures and Tables

**Figure 1 brainsci-12-00485-f001:**
[figure not shown]
Flowchart illustrating the design of the substudy integrated within the Music Interventions for Dementia and Depression in ELderly care (MIDDEL) trial. * In the CHUs in the combination group (GMT + RCS), no saliva samples were collected.

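### For saliva and stress-VAS outcomes the article claims four groups and change from baseline, but there are three saliva arms, no scheduled pre-course measurement, and no named contrast against book reading

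*Protocol article*

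**What the plan says.** **Arms.** Section 2.1 states: "For the part of the substudy addressing immediate effects using saliva samples, only three arms (GMT, RCS, control group) were included". The Figure 1 caption confirms it: "In the CHUs in the combination group (GMT + RCS), no saliva samples were collected". Sections 2.2 and 2.7 agree.

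**Visits.** Sections 2.6.3, 2.6.4 and 2.7 place saliva and the VAS at T1, T3 and T6, with one pre-session and two post-session measurements each time. Neither is scheduled at T0. On timing in the music arms, section 2.6.3 says: "The assessment took place at T1 (within 1 month after the music interventions started".

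**Analysis.** The last paragraph of section 2.11 opens with salivary cortisol (SC) and α-amylase (SAA). It promises a description of their response, then says the design can account for "between-group variation (including differential responses in four groups) and within-group variation (changes in participants between 3months, 6 months, and baseline". The parallel sentence in section 2.10.2 reads "between-group variation (including differential responses in three groups" and also refers to baseline. Beyond the description, section 2.10.2 plans a correlation of biomarker response with MADRS change.

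**Contrasts.** Section 2.9 says the main effects in the substudy are tested as "GMT versus no GMT and RCS versus no RCS so that all participants with available data could be used in each test". Section 2.10.1 writes these contrasts out for hair cortisol and the PSS-10.

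**Diurnal course.** The Introduction states: "Cortisol concentrations then decrease throughout the day, whereas α-amylase increases".

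**The concern.** Three statements do not fit the saliva and VAS data.

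1. The two parallel sentences disagree on the number of groups, and the count of four, in the saliva paragraph, contradicts the design.
2. Both sentences refer to change from baseline, but these outcomes have no T0 value. The sentence in 2.10.2 is hard to read as a summary of the whole substudy, because its count of three fits only the saliva arms.
3. The factorial wording in section 2.9 carries no restriction to the outcomes that have all four arms.

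The article also commits only to a description of the pre-to-post response. The hypothesis in section 2.6.3 is that music attenuates SC, which is the direction in which cortisol moves anyway during an afternoon. The book-reading sessions exist to separate the two, yet no saliva contrast explicitly uses them. An analyst following the text could therefore choose a reference value, a comparator and an effect measure that answer different questions.

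**Working it through.** **1. Design against wording**

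| | Hair cortisol, PSS-10 | Saliva, VAS |
|---|---|---|
| Arms | GMT, RCS, GMT + RCS, control | GMT, RCS, control (VAS is completed on saliva days) |
| Visits | T0, T3, T6, T12 | T1, T3, T6 |
| Value scheduled before the course | yes (T0) | none |
| Value before each session | not applicable | yes |

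Four groups with change from baseline describes the left column. It appears in a paragraph about the right column. With two sessions a week (section 2.4), a T1 window of about four weeks allows up to about 2 × 4 = 8 sessions around the first sample.

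**2. The article's own figure**

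Inputs from section 2.9: 160 analysed, average cluster size 8, ICC 0.01, two-sided 2.5%, 80% power.

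- Design effect = 1 + (8 − 1) × 0.01 = 1.07.
- Effective N = 160 / 1.07 = 149.5, or 74.8 per side.
- Two-sample t-test: detectable d = 0.509 (normal approximation 0.504).

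The stated 0.51 is reproduced, for 80 versus 80. That split needs all four arms.

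**3. What the factorial contrast would estimate in three arms**

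Let δG and δR be the effects of GMT and RCS against control, with equal arms. Without the combined arm, no GMT consists of RCS and control, with mean effect (δR + 0)/2. A pooled comparison therefore estimates

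δG − δR/2.

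If the two effects are equal, this is half of either. The 2×2 model with interaction has four parameters but only three cells (design-matrix rank 3), so the combined or interaction term cannot be estimated.

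**4. Size in the three saliva arms**

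Assumption: 50 per arm less 20% = 40 analysed, with the same design effect (40 / 1.07 = 37.4 effective per arm), two-sided 2.5%, one occasion and no covariate adjustment.

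- Music arm versus control, 40 versus 40: detectable d = 0.73; power at d = 0.51 is 47%.
- Pooled, 40 versus 80: detectable d = 0.62.
- Pooled contrast with a true GMT effect of 0.51:

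| RCS effect (assumed) | Pooled contrast | Power |
|---|---|---|
| 0 | 0.51 | 61% |
| 0.25 | 0.51 − 0.125 = 0.385 | 37% |
| 0.51 | 0.51 − 0.255 = 0.255 | 16% |

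- If saliva exclusions leave 32 or 24 per arm (assumed), the pairwise detectable d is 0.82 or 0.95.

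**5. Time span of one set of samples**

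Ten minutes before the session (Figure 2 footnote), 45 minutes of session (sections 2.4 and 2.5) and 60 minutes after: 10 + 45 + 60 = 115 minutes. Starting near 15:00 makes sessions comparable, but it does not remove drift within those 115 minutes. An unadjusted within-arm change includes that drift; a difference between arms sampled at the same time of day does not.

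**The case against.** The strongest reply is that most of this is a wording slip in exploratory secondary outcomes. Much of it stands.

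- The factorial contrasts are written out only for hair cortisol and the PSS-10, and the power calculation uses all four arms. A reader might infer that the article plans factorial tests, or claims d = 0.51, for saliva. It does not say so. Only the unrestricted wording of section 2.9 leads there.
- Dilution needs a pooled comparator. A three-level arm factor, or separate GMT and RCS indicators with control as reference, gives undiluted contrasts. Only the combined term is strictly lost.
- A reader might infer that T1 will serve as baseline, so that early treatment effect is subtracted. No section calls T1 baseline, and T0 and T1 are kept apart throughout.
- Every visit has a pre-session sample, so the immediate response is well defined.
- Book-reading sessions matched on group size, duration and time of day, together with the afternoon sampling window, are a sound design answer to diurnal drift. Nothing says that a within-arm fall will be reported as a music effect.
- Model detail may sit in an analysis plan that is not shown, so its absence is no fault.

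This does not remove the contradiction over the number of groups, or the reference to a baseline that these outcomes lack. Nor does it supply a stated comparison for which the book-reading arm is used.

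**Conclusion.** The point holds as a defect in what the article states. For saliva, four groups is wrong. For saliva and VAS, change from baseline is undefined. The substudy-wide factorial wording needs a boundary. The design itself is adequate: three arms, a pre-session value at each visit and a matched control session support a valid comparison, and the text should name it.

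The possible distortion is conditional. With a pooled comparator and equal arms, the GMT estimate falls short by half the RCS effect, so the loss runs from nothing (no RCS effect) to half (equal effects). The detectable effect of about 0.73 is a guide only. It rests on 40 per arm, ICC 0.01 and a single unadjusted occasion. Repeated measures and pre-session adjustment would improve it, and saliva exclusions would worsen it.

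The outcomes are secondary and exploratory, so this should be corrected but does not threaten the co-primary analysis.

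**What to change.** 1. In section 2.11, state three groups for saliva and VAS, in line with section 2.10.2.
2. In both sections, replace baseline for these outcomes with the same-session pre-session value, and treat T1 as the first outcome occasion. State that pre-post refers to the session.
3. Name the comparison: the post-session value (SAA at 15 minutes, SC at 60 minutes, and the VAS), adjusted for the pre-session value, as GMT versus book reading and RCS versus book reading. Fit it over T1, T3 and T6 with resident and CHU effects.
4. In section 2.9, limit the factorial tests and d = 0.51 to hair cortisol and the PSS-10. If a precision figure for saliva is wanted, give the single-occasion 0.73 with its assumptions.

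The cost is a few sentences and a standard mixed model. No extra samples or visits are needed. The Data Availability statement says data are still to be collected, so the change can be made before any analysis.

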## 3. Discussion

To the best of our knowledge, this is the first exploratory study assessing the effect of repeated music interventions (GMT and RCS) on chronic and acute stress using samples of HC, SC, and SAA in care home residents with dementia and depressive symptoms in the context of the large, multinational cluster-randomized controlled MIDDEL trial.

The collection of SC, SAA, and HC in care home residents with dementia might come with several specific challenges, such as apraxia, reduced saliva production because of aging, comorbidity, anticholinergic medication, and neurological/cognitive dysfunction in general. In the design and execution of the current study, we considered recommendations of previous studies. Firstly, levels of SC and SAA change over the lifespan [32]. An important consideration is the finding that the use of drugs, such as antidepressants and analgesics, can lead to insufficient saliva flow [32]. Several studies found that specific types of drugs might affect basal SC concentrations. Other aspects that can influence SC and SAA are food and consumption, alcohol and tobacco use, sleep, and exercise. A recent study found that physical frailty may also influence SC, although people with severe dementia were excluded [53]. Important potential confounders are: age, sex, somatic conditions (both somatic and acute) and related regular medication, smoking status, food and drink consumption (in the past hour), alcohol consumption (in the past 24 h), physical activity (in the last hour), and sleep (awakening time and napping in the past hour) [32]. Confounders associated with the outcomes (*p* < 0.05) were statistically controlled for.

Secondly, when collecting saliva samples, it is recommended to consider the sampling technique. The amount of saliva and SAA can be affected by the way samples are collected: stimulated samples by chewing on a small roll of cotton or unstimulated by passively drooling into a tube [5,53]. As the salivary flow rate can be limited in the target group because of aging and medication use, the use of a cotton roll (Salivette) was preferred. Another recommendation to better understand interactions is to include different types of biomarkers and multiple data collection time-points [15,16]. Ideally, cortisol concentrations are measured with a cortisol awakening response (CAR), with measurements up to seven times a day for two consecutive days. However, this is not the main question of this exploratory substudy; therefore, a more minimalistic design with three measurements on day one was chosen. Similar to other studies assessing changes in biomarkers in response to music (therapy) [46,54], in the current study, SC and SAA levels were assessed with multiple measurements, pre- and post-session. This will provide insight into changes within and between residents as a result of the music intervention.

Lastly, when designing a study assessing stress-related biomarkers, the timing of assessment, sampling periods, and consideration of psychobiological interactions should be taken into account [27]. Furthermore, an explanation of the bodily mechanisms of the biomarkers under investigation should be provided, thereby underlining the significance of testing these specific biomarkers [28]. Describing how the hormone is produced, how its levels are increased or decreased, and what its impact is on the body and the immune system is crucial to be able to put results and its relevance into perspective [28]. Moreover, the types of music should be clearly defined to be able to attribute changes in the biomarkers measured to a specific aspect of the music intervention, such as mode of delivery. This is the case in the music interventions offered in the MIDDEL trial.

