### 2.3. Randomization

Participants that were part of the MIDDEL trial were therefore randomized with their CHU to one of four groups: GMT, RCS, GMT plus RCS, or the control group. Randomization took place at the central study office after the completion of baseline assessments, using a computer-generated randomization list with a block size of four.

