### 2.5. Control Condition

The book reading served as a control condition for residents in the standard care group at T1 (within 1 month after completion of baseline assessment) and at T3 (3 months) and T6 (6 months). The control condition was similar to the music sessions in terms of group size, duration, and time of assessment. Hence, every book reading session took place around 15:00 h in the afternoon. All participating residents from the CHU participated in the book reading session. This session lasted 45 min. The book reading session was organized and supervised by either a volunteer, research assistant, research nurse, or care staff. This can also be the responsibility of one of the persons collecting samples before and after the session. The book reading session has an interactive character and functions as a social activity. A range of reading activities can be selected, such as reading local news stories, short stories, talking about headlines, and flipping through a magazine with pictures. Residents may read themselves or with the guidance of the supervisor if necessary. To illustrate, residents can read the paper and talk about headlines, whereas residents unable to read can flip through a magazine with pictures.

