### 2.7. Data Collection Procedures

Biomarkers were collected throughout the trial to assess the immediate and longer-term effects of repeated music interventions on chronic and immediate stress in care home residents with dementia and depressive symptoms (Figure 2). In Figure 2, the stress assessments of the substudy are presented within the assessment schedule of the MIDDEL trial. Hair samples were collected in all groups at T0, T3, T6, and T12 to assess physiological changes in chronic stress. Saliva samples were collected in the RCS, the GMT, and the control group at T1, T3, and T6. Saliva samples were collected just before, 15 min, and 1 h after the intervention to assess the immediate intervention effects. The group GMT plus RCS were only included to assess the longer-term effect of repeated music intervention on (chronic) stress.

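### Adjustment covariates are picked by a p < 0.05 association with the outcome, from a list about half of which is post-randomisation for saliva; this makes the model data-dependent and can attenuate the treatment effect

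*Protocol article*

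**What the plan says.** Section 3 (Discussion) gives the candidate list. It opens "Important potential confounders are: age, sex, somatic conditions (both somatic and acute) and related regular medication, smoking status", continues with recent food and drink and alcohol, and ends with "physical activity (in the last hour), and sleep (awakening time and napping in the past hour". The selection rule follows directly: "Confounders associated with the outcomes (*p* < 0.05) were statistically controlled for". It is not restricted to particular outcomes.

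The timing is set elsewhere. Section 2.3: "Randomization took place at the central study office after the completion of baseline assessments". Section 2.7: "Saliva samples were collected in the RCS, the GMT, and the control group at T1, T3, and T6". On each of those days saliva is taken "just before, 15 min after, and 60 min after the music/book reading session" (section 2.6.3).

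Section 2.4 gives a session length of about 45 minutes and includes movement among the components of GMT. Sections 2.10.2 and 2.11 expect amylase to respond at 15 minutes and cortisol at 60 minutes.

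Sampling time of day is not among the candidates. Section 2.6.3 handles it by scheduling: "between 12.00 and 17.00 h, preferably at 15.00 h, to minimize any confounding effects of the diurnal hormonal rhythm". Section 2.5 says that "every book reading session took place around 15:00 h in the afternoon".

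**The concern.** There are two separate problems.

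**Selection by outcome p-value.** Units are randomised, so the listed factors do not systematically confound the arm comparison. A baseline factor may still be worth adjusting for, to gain precision or to deal with chance imbalance among about 20 units, but that choice should be made before the outcome is seen. Under the stated rule the covariate set depends on the outcome data and can differ between outcomes and visits. The adjusted effect then has no fixed definition.

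**Post-randomisation candidates.** If the intervention changes a covariate and the covariate affects the outcome, adjustment takes that part out of the estimate. What remains is a direct effect and not the effect of being assigned to music. The rule makes this more likely, because a covariate on the causal path is by construction associated with the outcome and so tends to pass the screen. The Discussion itself names exercise among the influences on salivary cortisol and amylase.

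At stake is the interpretation of the adjusted saliva comparisons. As the rule refers to the outcomes in general, it also puts the models for hair cortisol and PSS-10 in doubt.

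**Working it through.** **1. The plan's own figure.** Section 2.9 gives a detectable effect of d = 0.51 with 160 participants, ICC 0.01, cluster size 8, two-sided 2.5% and 80% power. Design effect = 1 + (8 − 1) × 0.01 = 1.07. Effective N = 160 / 1.07 = 149.5. Solving the two-sample t-test gives d = 0.509, so the figure reproduces. It includes no covariates, and nothing below changes it.

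**2. Composition of the list.**
- Baseline or largely stable: age, sex, somatic conditions, regular medication, smoking status (5).
- Recent behaviour: food and drink, alcohol, physical activity, awakening time, napping (5).

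That is 5 of 10 counted singly, or about 4 of 8 or 9 as the list groups them. All saliva days follow randomisation, so the second group is post-randomisation for saliva.

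**3. How often irrelevant candidates enter.** Assuming independent candidates unrelated to the outcome, P(at least one selected) = 1 − 0.95^k. For k = 10 this is 0.40; for k = 8 it is 0.34. This measures instability of the model, not error inflation.

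**4. Overlap of last-hour activity with the session.**
- Pre-session sample: the preceding hour contains none of the session.
- +15 min sample: 15 + 45 = 60 min, so the preceding hour contains the whole session.
- +60 min sample: the preceding hour begins when the session ends.

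The overlap therefore falls on the time point at which amylase is expected to respond. It arises only if the item is recorded for that sample. Section 2.7.2 describes one short questionnaire on adherence before collection and does not say whether it is repeated.

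**5. Size, under assumptions not in the document.** Let treatment shift the covariate by a SD, and let the covariate have slope b on the outcome. Full adjustment changes the estimate by a × b: 0.3 × 0.2 = 0.06, 0.5 × 0.3 = 0.15, 0.8 × 0.4 = 0.32 SD.

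The p < 0.05 rule was simulated with 40 v 40 participants (50 per arm less 20%), one candidate, ordinary least squares, two-sided 5%, no clustering, and 2,000 runs per row. The true total effect was set at 0.51 SD purely for illustration.

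| a | b | Candidate selected | Mean estimate, unadjusted | Mean estimate, with rule | Power, unadjusted | Power, with rule |
|---|---|---|---|---|---|---|
| 0 | 0.3 | 74% | 0.52 | 0.51 | 0.64 | 0.65 |
| 0.3 | 0.2 | 53% | 0.52 | 0.47 | 0.62 | 0.55 |
| 0.5 | 0.3 | 87% | 0.51 | 0.37 | 0.62 | 0.38 |
| 0.8 | 0.4 | 99% | 0.51 | 0.19 | 0.60 | 0.13 |

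With no true total effect (4,000 runs), the rejection rate under the rule is 0.051 for a = 0, b = 0.3. For a = 0.5, b = 0.3 it is 0.087, with a mean estimate of −0.13.

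The table has the path through the covariate running in the same direction as the total effect, which gives attenuation. If the two run in opposite directions, adjustment moves the estimate away from zero. The document does not give these directions.

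**The case against.** The strongest reply is that this is one sentence in the Discussion of a condensed article about an exploratory substudy. The listed factors are introduced as influences on saliva, a secondary outcome for which mainly a description of the response is promised. Items asked only before a session cannot carry that session's immediate effect. In the correlation analyses of biomarker response with MADRS change, which are not randomised comparisons, some of these factors could be genuine confounders.

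Most of this stands, and it limits the reach of the point. It does not remove it. The sentence is an explicit rule and not a detail left to an analysis plan, and it names the outcomes without restriction. Items recorded before the session can still carry effects that have built up by T3 or T6.

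Four stronger readings are tempting, but the document does not support them:

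- **That the list is mostly post-randomisation.** About half of it is baseline or stable.
- **That clock time is the one driver of saliva levels the plan recognises, and that it was left out.** The Discussion names several drivers, including drugs, food, alcohol, tobacco, sleep and exercise. Awakening time is on the list.
- **That the arms differ in sampling time.** The 12.00 to 17.00 h window covers music and book-reading days alike, sessions near 15.00 h were chosen, and section 2.5 matches the control on time of assessment. With a 15.00 h start, a 45-minute session and the first sample ten minutes beforehand (Figure 2 legend), one resident's samples fall at about 14.50, 16.00 and 16.45 h. Part of the window is needed for that alone.
- **That the screen by itself gives standard errors that are too small.** When treatment does not affect the candidate, the simulated type I error is 0.051.

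**Conclusion.** The point holds in a limited form. The article fixes a covariate rule that depends on the outcome data and draws on a list in which about half the items are post-randomisation for saliva. Following it leaves the adjusted model undetermined until the data are seen, and it can attenuate the treatment effect where the intervention changes a selected item. Last-hour activity at the +15 min sample is the clearest candidate, on condition that it is recorded for that sample.

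The size is not known. The shift of 0.06 to 0.32 SD rests entirely on assumed paths and is zero if treatment leaves the covariate unchanged. Expressing it as a share of 0.51 would mislead: that figure belongs to the 160-participant main comparisons, not to the three-arm saliva analysis. Attenuation is a possibility created by the rule, not a demonstrated bias. The change is still worth making, because it costs almost nothing.

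**What to change.** - Delete the p < 0.05 selection rule.
- Prespecify baseline covariates for every outcome, for example the baseline value where one is collected, age, sex and country. The hair cortisol and PSS-10 models already include baseline stress (section 2.10.1).
- Keep same-day and post-session behaviours (food and drink, alcohol, activity, awakening time, napping) out of the main models. Use them only in a labelled sensitivity analysis, and state for each item when it is recorded.
- For the within-session saliva response, adjust for the pre-session value. State that at T1, T3 and T6 this value is itself post-randomisation, so the analysis estimates only the immediate effect of that session and not any effect accumulated since randomisation.
- Optionally add clock time of sampling to the saliva models as a precision covariate, because a five-hour window is permitted. Scheduling near 15.00 h in both conditions already limits its influence.

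The cost is some wording and a few degrees of freedom, plus one field on the sampling form if clock time is used and not already recorded. The article states that data are still to be collected, so the covariates can be fixed before any outcome is analysed.
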